### Outcomes

The outcome measurements will be made by an examiner calibrated according to the guidelines of DC/TMD criteria. The DC/TMD instruction video has been peer-reviewed and published [22]. Self-study guidelines and description of supervised skill development have also been described. The outcome measurements will be made at baseline and at the time points of 24 hours, 7 days, 28 days, and 3 months.

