### Participation Timeline

Each eligible patient will be participating in the trial for 3 months, 1 year from their visit (baseline). The total number of visits will depend on the study arms to which the participants are allocated, but the outcome measurements will be recorded at 5 visits (baseline, 24 hours, 1 week, 28 days, and 3 months; Figure 2 and Table 1).

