### Compliance With Trial Treatment

The follow-up visits of the individual are important for the trial. Compliance to visit the dental clinic at designated intervals is done by telephonic and email reminders to the individuals. If the individual has missed the appointment or wants to reschedule, then it is rescheduled within +/– 2 days. If the individual misses two rescheduled appointments, then it is referred as noncompliance. The individual will be withdrawn from the study. However, if the individual completes 6 months and becomes noncompliant for the next 6 months, the person’s time of participation in the trial will be counted and will be used for analysis.

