### Analysis Population and Missing Data

We will report reasons for withdrawal for each randomization group and compare the reasons qualitatively. The effect that any missing data might have on results will be assessed via sensitivity analysis of augmented data sets. Dropouts will be included in the analysis by using multiple imputation methods for missing data. Excluding patients from the analysis who violated the research protocol (did not get their intended treatment) can have significant implications that impact the results and analysis of a study. If the attrition loss is less than 15%, a per protocol analysis will be carried out; otherwise, “intention to treat” will be performed.

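### The compliance rule ties use of a noncompliant patient's data to completing 6 months, which matches no listed visit and appears to conflict with imputing dropouts

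*Protocol article*

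**What the plan says.** **Noncompliance (Protocol article, Compliance With Trial Treatment).** The definition is "If the individual misses two rescheduled appointments, then it is referred as noncompliance". The consequence follows: "The individual will be withdrawn from the study". An exception comes next, introduced by the word However: "if the individual completes 6 months and becomes noncompliant for the next 6 months", in which case the person's "time of participation in the trial will be counted and will be used for analysis".

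**Visits.** The Outcomes section states: "The outcome measurements will be made at baseline and at the time points of 24 hours, 7 days, 28 days, and 3 months". The Abstract, Participation Timeline and Table 1 give the same end point, and Strengths and Limitations describes follow-up as 3 months after the intervention.

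**Length of follow-up elsewhere.** Participation Timeline says "Each eligible patient will be participating in the trial for 3 months", but the same sentence goes on to give 1 year from baseline. Data Collection Methods, Table 3 in Statistical Methods and the interim analysis in Data Monitoring all refer to 12 months. None of them lists a visit after 3 months.

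**Missing data (Analysis Population and Missing Data).** "Dropouts will be included in the analysis by using multiple imputation methods for missing data". No minimum time in the trial is attached. The same section then chooses per protocol if attrition is below 15%, and intention to treat otherwise.

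**The concern.** An exception that begins with However limits the sentence before it. If participation is used for analysis when 6 months have been completed, the natural inference is that it is not used otherwise. That raises two problems: the threshold lies beyond the last listed visit, and the implied exclusion runs against the plan to include dropouts by imputation. Two analysts who each followed one section could build different analysis sets from the same patients.

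The stake is the comparison of arms. According to the Blinding section, neither patients nor treating dentists are blinded, so failure to attend may differ between the prosthesis arms and the counselling arms and may be related to pain. A noncompliant patient's early pain scores are the most direct information for imputing that patient's later ones. Setting them aside would weaken the imputation where it is most needed.

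**Working it through.** The plan computes no figure for this rule, so there is none to reproduce. The check compares the sections and sizes the group affected.

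**1. Can the exception be met on the listed schedule?**

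Inputs: threshold 6 months and rescheduling window of plus or minus 2 days (Compliance With Trial Treatment); last visit 3 months (Outcomes, Table 1); prosthesis visit at 2 weeks (Table 1). One month is taken as 30.44 days.

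- Threshold: 6 × 30.44 = 182.6 days.
- Last visit counted from baseline: 3 × 30.44 = 91.3 days.
- Last visit counted from the 2-week prosthesis visit: 91.3 + 14 = 105.3 days.
- Smaller gap: 182.6 − 105.3 = 77.3 days. The 2-day window does not close it.

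A Table 1 footnote allows several prosthesis visits, so some patients may start the 3-month clock later than 2 weeks. That does not rescue the exception. Its second half requires noncompliance during months 6 to 12, noncompliance is defined by missed appointments, and no appointment is listed in that period. On the listed schedule the exception applies to no patient.

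**2. Does a 12-month follow-up remove the problem?**

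The wording adds up to 6 + 6 = 12 months, so the exception does fit the 12-month version and could then be reached. Patients who become noncompliant before 6 months still fall outside it. All four listed follow-up readings (24 hours, 7 days, 28 days, 3 months) precede month 6.

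**3. One patient under each section.** Take a patient who attends to day 28 and then becomes noncompliant.

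| Section | 3-month follow-up | 12-month follow-up |
|---|---|---|
| Compliance With Trial Treatment | withdrawn; exception out of reach; appears not used | withdrawn before 6 months; appears not used |
| Missing data, sentence on dropouts | included by multiple imputation | included by multiple imputation |
| Missing data, attrition below 15% | per protocol; may be left out | per protocol; may be left out |
| Missing data, attrition 15% or more | intention to treat; included | intention to treat; included |

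The first two rows disagree under either length. The third row shows that the missing-data section is not fully settled within itself.

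**4. How many patients?**

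Inputs: projected loss of at most 5% a year (Data Collection Methods); 300 patients (Sample Size). The protocol gives no separate noncompliance rate, so the projected loss is assumed to be a ceiling for it.

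- Over a year: 0.05 × 300 = 15.
- Over 3 months at a constant rate (an assumption): 15 × 3/12 = 3.75, about 4.
- Attrition switch: 0.15 × 300 = 45. The projected 15 is below it, so the per protocol branch is the one to expect.

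The patient in step 3 has a baseline reading and three follow-up readings at stake.

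**The case against.** **The threshold is not unreachable in every reading.** Four places in the protocol speak of a year or 12 months, and the 6 + 6 month wording matches them. A reader might infer that nobody can ever meet the condition, but the documents support that only for the 3-month schedule. This part of the point is a consequence of the unresolved follow-up length. That objection stands.

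**Discarding is not stated.** The compliance section says that the patient is withdrawn; it does not say that readings already taken are dropped. One could treat every withdrawn patient as a dropout and apply imputation, in which case nothing is lost. This also stands: it is tempting to call the two sections a flat contradiction, but the exclusion is inferred. What the objection leaves unexplained is why an exception permitting use for analysis would be needed if everyone's data were used anyway.

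**The missing-data section has its own tension.** At the projected loss the per protocol branch applies, and it may leave noncompliant patients out regardless of the compliance section. This is correct, and a repair that ignored the switch would create a new conflict.

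**Counting participation time.** A reader might infer that a person-time analysis was intended and is missing from Table 3. The phrase is too loose to carry that, and the point does not rely on it.

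**Conclusion.** The concern holds in a limited form. As written, the 6-month condition on data use matches no listed visit and fits only a 12-month follow-up that the visit schedule does not provide. Under either length, the handling of patients noncompliant before 6 months is at odds with the sentence on imputing dropouts, on the natural reading of the exception rather than on an explicit statement.

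The size is small to moderate: at most about 15 of 300 patients, or about 4 if the annual rate is prorated. Both figures take projected loss to follow-up as the ceiling for noncompliance, and the smaller also assumes a constant rate.

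No bias in millimetres of pain is claimed, because the documents give neither noncompliance by arm nor the pain of noncompliant patients. With assumed noncompliance of 10% v 3% and pain 20 mm worse in those patients, the shift would be 0.10 × 20 − 0.03 × 20 = 1.4 mm. All three inputs are assumptions. The result is the effect of excluding noncompliant patients entirely, not the cost of losing their early readings, and should not be cited as the latter.

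**What to change.** 1. In Compliance With Trial Treatment, delete the 6-month condition on use of data. Replace it with a statement that all outcome readings obtained from every randomised patient are used, in the arm allocated, and feed the multiple imputation model, whatever the length of participation. This concerns data use only and leaves the conduct of withdrawal as it is.
2. In Analysis Population and Missing Data, state that this governs the primary analysis regardless of the 15% attrition switch, with per protocol reported as a sensitivity analysis. Without this sentence the first change would conflict with the switch.
3. Reconcile 3 months with 12 months across Participation Timeline, Data Collection Methods, Compliance With Trial Treatment, Table 3 and Data Monitoring. The first two changes work under either length.

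The cost of the first two changes is one replaced sentence and one added sentence, with no extra data and no extra visits. The third is an edit across sections once the sponsor has settled the follow-up length.

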### Data Forms and Data Entry

This may be done at a center or at the participating site where the data originated. Original study forms will be entered and kept on file at the participating site. Participant files are to be stored in numerical order and stored in a secure and accessible place and manner. Participant files will be maintained in storage for a period of 3 years after completion of the study.

All forms related to study data will be kept in locked cabinets. Access to the study data will be restricted. All reports will be prepared such that no individual patient can be identified. The study sites will send 6-month email reports with information on missing data, missing forms, and missing visits.

### Statistical Methods

The effectiveness of pain reduction within each arm and between each group will be analyzed using analysis of variance. The details of the analysis are explained in Table 3.

**Table 3 table3:** List of proposed analysis for trial results.^a^

Variable/outcome			Hypothesis		Outcome measure		Methods of analysis
Effectiveness of reduction of pain: within each arm			Intervention improved outcome from baseline to 12 months		Per person reduction of VAS^b^ score and GCPS^c^ (proportion or mean)		Chi-square methods or ANOVA^d^
Effectiveness of reduction of pain: between group 1, group 2, and group 3			Intervention improved outcome from baseline to 12 months		Per person reduction of VAS score and GCPS (proportion or mean)		Chi-square methods or ANOVA

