### Sequence Generation

The selected patient for trial will be randomly allocated to either the intervention arm or the control arm of their group, as per computer-generated randomization, schedule stratified, based on the type of group it belongs. The selected individuals will be allocated in equal probabilities to the intervention and control groups by stratified randomization. Stratified randomization is achieved by performing a separate randomization procedure within each of the two strata of participants. This will ensure that the numbers of participants receiving each intervention are closely balanced within each stratum. Treatment assignments are then made from separate randomization lists created in advance of the trial for each stratum.

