**Subgroup analysis**							
	Effectiveness of reduction of pain: between group 1, group 2, and group 3	Intervention improved outcome from baseline to 12 months		Per person reduction of VAS score and GCPS (proportion or mean)		Regression methods with appropriate interaction term	
	Between posterior teeth rehabilitation vs anterior teeth rehabilitation	Number of teeth affects effectiveness of outcome		Per person reduction of VAS score and GCPS (proportion or mean)		Chi-square methods	
	Upper vs lower teeth	Position of edentulism affects the effectiveness outcome		Per person reduction of VAS score and GCPS (proportion or mean)		Chi-square methods	
	Duration of edentulism	Duration of edentulism affects pain outcome		Per person reduction of VAS score and GCPS (proportion or mean)		Chi-square methods	
	Number of quadrants	Number of quadrants affects the effectiveness outcome		Per person reduction of VAS score and GCPS (proportion or mean)		Chi-square methods	

^a^In all analyses, results will be expressed as coefficient, SEs, corresponding 95%, and associated *P* values. Goodness of fit will be assessed by examining the residuals for model assumptions and chi-square tests for goodness of fit.

^b^VAS: visual analog scale.

^c^GCPS: Graded Chronic Pain Scale.

^d^ANOVA: analysis of variance.

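### Table 3 fixes the main pain analysis as ANOVA or chi-square on VAS reduction, with no adjustment for baseline VAS and no intervention-versus-control row

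*Protocol article*

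**What the plan says.** Statistical Methods states: "The effectiveness of pain reduction within each arm and between each group will be analyzed using analysis of variance". It refers to Table 3 for the details. Table 3 has two main rows for pain, one within each arm and one between groups 1, 2 and 3. For both, the method is "Chi-square methods or ANOVA" and the outcome measure is the individual reduction in VAS and GCPS, taken as a mean or a proportion. Neither row names a covariate, and neither is a comparison of intervention with control. The only regression is a subgroup row across the three groups: "Regression methods with appropriate interaction term".

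The data needed for adjustment are already planned. Under Outcomes: "The outcome measurements will be made at baseline and at the time points of 24 hours, 7 days, 28 days, and 3 months". Under Allocation Concealment Mechanism, the code is released only after the baseline measurements are complete, so baseline VAS is a proper pre-randomisation covariate. Under Sequence Generation, allocation is 1:1 and stratified by type of edentulous group: "Treatment assignments are then made from separate randomization lists created in advance of the trial for each stratum".

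The Hypothesis section says that rehabilitation will reduce pain compared with patients who are not rehabilitated. That is a between-arm claim.

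**The concern.** Subtracting baseline fixes its coefficient at 1, whereas ANCOVA estimates the coefficient from the data. Where the true slope is below 1, the change score over-corrects. It then carries more noise than it needs to, and in any one trial the arm that happens to start with more pain tends to show the larger fall. ANCOVA removes this dependence on chance imbalance and narrows the interval, using a measurement the trial already takes on every patient.

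This bears on the primary objective. The between-arm contrast that would answer the hypothesis has no row in Table 3, so no analysis is fixed for it. If the method of the existing rows were carried over to it, the trial would estimate its main pain effect less precisely than its own data allow, with 50 patients per arm in each edentulous group. The proportion option with a chi-square test would discard more information still.

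**Working it through.** **1. The plan's own figure.** Inputs from Sample Size: effect size 0.77, power 80%, alpha .05, 22 per group. Sidedness is not stated. For two equal groups, n per group = 2(z_alpha + z_power)²/0.77².
- One-sided: 21 by the normal formula, 22 with the t distribution. The stated 22 is reproduced.
- Two-sided: 27 (normal) or 28 (t). At 22 per group, two-sided power is 70% (t).

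This effect size was set for EMG, and the trial plans 50 per arm. The comparison below therefore uses 50, and treats any pain effect as an assumption.

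**2. Variance of the two analyses.** Let the baseline and follow-up SDs be S0 and S1, with correlation rho.
- Change score: S1² + S0² − 2·rho·S0·S1
- ANCOVA: S1²(1 − rho²)
- Difference: (S0 − rho·S1)², which is never negative and is zero only when rho·S1/S0 = 1.

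With S0 = S1 = SD, these become 2(1 − rho)SD² and (1 − rho²)SD². The ratio of ANCOVA to change score is (1 + rho)/2.

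| rho (assumed) | ratio | variance reduction |
|---|---|---|
| 0.3 | 0.65 | 35% |
| 0.5 | 0.75 | 25% |
| 0.7 | 0.85 | 15% |

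**3. Power.** Noncentral t, two-sided .05, with d in change-score SD units. For ANCOVA the effect becomes d/√((1 + rho)/2), with one fewer degree of freedom. At rho 0.5 and d = 0.5, this is 0.5/√0.75 = 0.577.

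| Comparison | d | Change score | ANCOVA, rho 0.7 | rho 0.5 | rho 0.3 |
|---|---|---|---|---|---|
| 50 v 50 | 0.5 (assumed) | 69.7% | 76.6% | 81.5% | 86.7% |
| 50 v 50 | 0.77 (EMG figure) | 96.8% | 98.5% | 99.3% | 99.7% |
| 150 v 150 | 0.3 (assumed) | 73.6% | 80.2% | 84.9% | 89.5% |

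At rho 0.5, the gain is at least 5 points for d of about 0.23 to 0.68 at 50 v 50, and about 0.13 to 0.39 at 150 v 150.

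**4. Stratum.** Within one edentulous group the stratum is constant, so there is nothing to adjust for. In a pooled 150 v 150 contrast, suppose strata explain a share f of the residual variance. The standard error then falls by the factor √(1 − f): 0.99 at f = 2% and 0.95 at f = 10%. The documents do not give f.

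**5. Proportion option.** A split of a normally distributed outcome at its median keeps about 2/π = 64% of the efficiency of comparing means.

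**6. Two points to settle before a model can be written.**
- Sequence Generation says "Stratified randomization is achieved by performing a separate randomization procedure within each of the two strata of participants", while Interventions and Table 2 have three edentulous groups.
- Table 3 tests improvement to 12 months, while Outcomes and Participation Timeline place the last outcome measurement at 3 months.

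**The case against.** The strongest reply is that the change score is sound. Randomisation makes it unbiased, it already uses baseline, and chance imbalance is reflected in its standard error. That stands: the point is one of efficiency. A reader might infer from the regression-to-the-mean argument that the planned analysis gives a biased or invalid answer, but nothing in the documents supports that.

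A second reply is that the article is condensed and covariates are usually left to the analysis plan. This holds in part. Silence on the stratum could be filled in later. The response variable and test for the pain rows are written down, however, so an ANCOVA on follow-up VAS would depart from Table 3 rather than add detail to it.

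A third reply concerns size. One could quote the gain at 22 per group, but the trial enrols 50 per arm, and the low two-sided power at 22 partly reflects sidedness. The Table 2 quotas of 20 are recruitment minima, not planned arm comparisons. At 50 v 50 and the only effect size in the document, the gain is 2.5 points (99.3 − 96.8). The larger gains depend on assumed pain effects. All of this stands.

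It is also tempting to fault the missing stratum term as strongly as the missing baseline. The documents do not support that: group is the factor itself in the between-group row and enters the subgroup regression, and a comparison within one group does not need it.

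**Conclusion.** The point holds as a recommended improvement. Table 3 commits the main pain analysis to a valid but less efficient method, and it gives no row to the contrast that the hypothesis requires.

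The variance saving of 15% to 35% rests on equal SDs and an assumed rho of 0.7 to 0.3. With unequal SDs the saving may be smaller or larger, and it vanishes when rho·S1/S0 equals 1. The effect on power is material for moderate pain effects (about 12 points at 50 v 50 with d = 0.5 and rho 0.5) and negligible if the pain effect is as large as 0.77. Because 0.77 comes from EMG and no VAS effect, SD or correlation is given, the documents cannot show which case applies. The stratum matters only for a pooled analysis, and its benefit there is probably small: about 1% to 5% of the standard error for the assumed 2% to 10% of variance explained.

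**What to change.** Add to Table 3 an explicit intervention-versus-control row for pain, analysed by ANCOVA. Follow-up VAS is the response, arm the factor, and continuous baseline VAS the covariate. Report the adjusted mean difference with its 95% CI. Use this model within each edentulous group. In any pooled 150 v 150 analysis, add the randomisation stratum as a covariate. Keep any analysis of proportions as supportive.

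Before writing the model, reconcile the two strata in Sequence Generation with the three groups elsewhere, so that the stratum term is defined. Also reconcile the 12 months in Table 3 with the 3-month last outcome visit, so that the response is defined.

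The change needs no new data, visits or patients. It costs wording and one to three degrees of freedom: one for baseline VAS, and two more if a three-level stratum is included. Settling the two inconsistencies is extra work, but any analysis of this trial needs it.

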### Trial Design

This trial is designed as randomized, as controlled, with a parallel arm, as blinded for outcome measurement, and with adaptive trial design.

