### Data Collection Methods

Each personnel will be trained centrally for the study requirements, standardization of examination and assessment of the outcomes and counselling for adherence, and the eliciting of information from study participants in a uniform reproducible manner. The data to be collected and the procedures to be conducted at each visit will be reviewed in detail. Each of the data collection forms and the nature of the required information will be discussed in detail on an item-by-item basis. Entering data forms, responding to data discrepancy queries, and general information about obtaining research quality data will also be covered during the training session. Once an individual is enrolled or randomized, the study site will make every reasonable effort to follow the individual for the entire study period of 12 months. It is projected that the rate of loss-to-follow-up on an annual basis will be at most 5%.

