### Data Monitoring

An interim analysis is performed on the primary end point (reduction in pain) when 50% of patients have been randomized and have completed the 12-month follow-up. The interim analysis will be performed by an independent statistician, blinded for the treatment allocation.

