### Strengths and Limitations of This Study

This study has the following strengths and limitations:

The study design (RCT) will provide evidence of prosthetic rehabilitation on the TMD.Patients with TMD are grouped based on their edentulous state as completely or partially edentulous, and partially edentulous patients are classified further based on the Kennedy classification. This ensures that the effect of different types of edentulism on TMD are assessed.EMG reading for recording the muscle activity is an additional quantitative outcome evaluation used to assess and evaluate the TMD.As the study has a follow-up period of 3 months after the intervention, we expect some amount of attrition.

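### Table 3 tests pain reduction at 12 months and the interim analysis waits for 12-month follow-up, but no pain measurement is scheduled after 3 months

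*Protocol article*

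**What the plan says.** **Measurement ends at 3 months.** The Outcomes section states: "The outcome measurements will be made at baseline and at the time points of 24 hours, 7 days, 28 days, and 3 months". The Abstract gives the same list. Participation Timeline counts five outcome visits, the last at 3 months, and the last column of Table 1 is the 3-month visit. Strengths and Limitations agrees: "As the study has a follow-up period of 3 months after the intervention, we expect some amount of attrition".

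**Analysis is set at 12 months.** In Table 3 (Statistical Methods), the within-arm row, the between-group row and the first subgroup row all read "Intervention improved outcome from baseline to 12 months", with VAS and GCPS reduction as the measure. The other subgroup rows name no time point. Data Monitoring places the interim analysis of pain reduction at the moment "when 50% of patients have been randomized and have completed the 12-month follow-up".

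**Other sections take one side or both.** Participation Timeline gives two lengths in one sentence: "Each eligible patient will be participating in the trial for 3 months, 1 year from their visit (baseline". Data Collection Methods says "the study site will make every reasonable effort to follow the individual for the entire study period of 12 months". Compliance With Trial Treatment has a rule for the case "if the individual completes 6 months and becomes noncompliant for the next 6 months".

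**The concern.** Pain reduction is the primary objective. A change from baseline to 12 months needs a 12-month value, and the schedule produces none. Multiple imputation, which the plan proposes for dropouts, does not help, because the value would be absent for every participant and there would be nothing observed to impute from.

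The time point actually analysed would therefore be settled outside the stated plan, possibly after data are in hand. Other rules inherit the doubt. The interim has no defined endpoint value. The compliance rule that retains a participant's time after 6 months cannot apply in a 3-month trial. The choice between per-protocol and intention-to-treat analysis turns on attrition measured over a period that is not settled.

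**Working it through.** **1. Time points side by side**

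| Section | Last or stated time point |
|---|---|
| Abstract, Methods | 3 months |
| Outcomes | 3 months |
| Participation Timeline, outcome visits | 3 months |
| Table 1, last column | 3 months |
| Strengths and Limitations | 3 months |
| Participation Timeline, length of participation | 3 months and 1 year |
| Data Collection Methods | 12 months |
| Compliance With Trial Treatment | 6 + 6 = 12 months |
| Table 3, the three rows with a time point | 12 months |
| Data Monitoring, interim | 12 months |

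Scheduled pain assessments later than 3 months: 0. The sections that speak of a year or 12 months extend participation or follow-up, but none of them adds an outcome visit.

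**2. When the interim would fall**

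The article gives no interim date to reproduce, so this step rests on assumptions.

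Inputs: recruitment from May 2021 to March 2023 (Abstract, Results); 300 patients (Sample Size); interim at 50%, so 0.5 × 300 = 150 patients (Data Monitoring). Assumptions: even accrual from 1 May 2021 to 31 March 2023, follow-up counted from entry, no loss.

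- Recruitment length: 365 + 334 = 699 days.
- Patient 150 enters at 699 / 2 = 349.5 days, on 15 April 2022.
- 12-month endpoint: 15 April 2022 + 365 days = 15 April 2023, 15 days after recruitment closes, with 300 of 300 enrolled.
- 3-month endpoint: 15 April 2022 + 91 days = 15 July 2022, which is day 440. Enrolled: 440 / 699 = 63%, or 0.63 × 300 = 189 patients.

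**3. How firm those dates are**

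- Start and end days: moving them within May 2021 and March 2023 puts the 12-month interim between 31 March and 30 April 2023, not before recruitment closes in any of these cases.
- Accrual shape: by 31 March 2022 even accrual gives 334 / 699 = 47.8%, about 143 patients. Seven more by that date (150 − 143) would bring the 12-month interim inside the recruitment period, though near its end.
- Start of the clock: if the 3 months run from delivery of the prosthesis, which Table 1 puts at 2 weeks or later, the 3-month interim moves to about 29 July 2022, with (440 + 14) / 699 = 65% enrolled.

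**4. Attrition horizon**

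Projected loss is at most 5% a year. Over 3 months the same rate gives 1 − 0.95^0.25 = 1.3%. Both are below the 15% threshold for choosing the analysis population, so on the projected rate the horizon would not change that choice. It matters only if loss is much higher than projected.

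**5. Sample size**

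The stated calculation is based on EMG and carries no time point, so choosing 3 or 12 months changes nothing in it.

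**The case against.** The best defence is that 12 months is a leftover and the intended contrast is baseline to end of follow-up, which makes the 3-month visit the natural reading. That has some force: it is too strong to say that analysts would be free to choose any of the four post-baseline visits. But the longer horizon appears in five sections, among them the interim trigger and a compliance rule built on two 6-month halves. A reader cannot tell from the article which horizon is the leftover.

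A second defence is that this is a condensed article. That would excuse an omission, but here two incompatible time points are stated.

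Some stronger inferences are tempting, and the article does not support them:

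- **That the interim can never trigger.** Participants are to be followed for 12 months, so the trigger can be reached by calendar time. What is missing is a pain value to analyse when it is.
- **That type I error rises to 8.3%.** That figure belongs to two unadjusted 5% tests, at half and at full information. The article states no test level for the interim and no intention to stop for efficacy.
- **That there is no stopping threshold, or that the phrase "and with adaptive trial design" is empty.** Boundaries and adaptation rules are commonly left to the full protocol or the analysis plan, neither of which is shown.
- **That a 12-month interim must come after recruitment closes.** This needs even accrual, and then holds by only 15 days.

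**Conclusion.** The contradiction stands and needs correction before any unblinded analysis. All three Table 3 rows that name a time point, and the interim analysis, call for a 12-month pain value that the schedule does not collect. This part rests on the text alone and needs no assumption.

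The interim dates are conditional on even accrual and follow-up counted from entry. Under those assumptions a 3-month endpoint gives an interim with about 37% of patients still to be enrolled (100% − 63%), while a 12-month endpoint gives one at about the close of recruitment, earlier if accrual is front-loaded.

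The article does not settle which horizon the sponsor meant, so either can be adopted provided the schedule and the analysis agree.

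**What to change.** Name one primary time point for VAS pain before any unblinded analysis, and align every affected section to it.

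**Cheap repair: 3 months, the last scheduled visit.**

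- Table 3: replace 12 months with 3 months in the three rows that name it.
- Data Monitoring: trigger the interim when 50% of patients (150) have the 3-month VAS.
- Participation Timeline and Data Collection Methods: state a single follow-up length of 3 months.
- Compliance With Trial Treatment: reconcile the 6 + 6 month rule with the chosen length rather than simply deleting it. It is the only sentence in that section that keeps data from participants who become noncompliant late, so the revised text should still keep data already collected from them.

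The cost is a protocol amendment with no new visits and no change in sample size. Changing the interim trigger is a change to the plan, not only to its wording. The conclusion on pain is then limited to 3 months.

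**Alternative: 12 months.** Add a 12-month pain assessment (VAS and GCPS) to Outcomes, Participation Timeline and Table 1, and correct the 3-month statements in the Abstract and the limitations. The cost is an extra visit and longer follow-up for every participant, plus an interim that could do little to limit enrolment.
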